# STUDY POPULATION

## 4.1 Population (base)

In the cross-sectional study, 200 pregnant women carrying a healthy, singleton fetus with a gestational age between 18 and 24 weeks, who visit the outpatient clinic in MMC Veldhoven or Diagnostic center Eindhoven, will be included. If any of the fetuses turn out to have a form of CHD, the data will be either excluded or analyzed in the case-cohort study.

In the case-cohort study, pregnant woman carrying a singleton fetus, with a gestational age between 18 and 24 weeks, with a known severe CHD will be included. We will include patients with the following CHD: Fallot’s tetralogy (possible with pulmonary atresia of stenosis), hypoplastic left heart syndrome, aortic stenosis, transposition of the great vessels, coartcation of the aorta and atrial ventricular septal defect. We chose these types because they are severe and have hemodynamic consequences if they do not get the proper treatment. Because of the low incidence of these types of CHD (see appendix I page 27), we believe it is impossible to gather more than 10 patients per CHD. Therefore, we will include 10 patients in every CHD group, leading to a total of 60 patients with 6 different forms of severe CHD. We believe that we will include 20 patients per participating center, thus 2 forms of CHD in every center. We believe this will be enough to detect any big differences between the fECG of the healthy fetuses and the fECG of the fetuses with CHD, but we are aware that more research will be needed in the future. Because the incidence in our medical center is low, collaboration with more than one center is needed.

## Inclusion criteria

In order to be eligible to participate in the cross-sectional study, a subject must meet all of the following criteria:

- Pregnant women carrying a healthy fetus
- Aged older than 18 years
- Gestational age between 18 and 24 weeks

In the case-cohort study, a subject must meet all of the following criteria:

- Pregnant woman carrying a fetus with a known severe CHD (Fallot’s Tetralogy,

hypoplastic left heart syndrome, aortic stenosis, pulmonary atresia, transposition of the great vessels, coartcation of the aorta and an atrial ventricular septal defect)

- Aged older than 18 years
- Gestational age between 18 and 24 weeks

## Exclusion criteria

A potential subject who meets any of the following criteria will be excluded from participation in this study:

- Multiple Pregnancies
- Insufficient understanding of Dutch language

## Sample size calculation

This will be the first study to investigate the clinical contribution of fECG for the diagnosis of severe CHD. We believe that a total of 200 patients will be enough to evaluate the normal range or value of the different segment intervals and amplitudes of the fECG, as described in the literature by Douglas G. Altman^10^. For the case-cohort study, we believe that a total of 10 patients per severe CHD will be enough for the evaluation and the comparison of the fECG of a healthy fetus and the fECG of a fetus with known severe CHD. No sample size calculation was used in the estimation of the size of the population for the case-cohort study, since this is a pilot study.

# 5. TREATMENT OF SUBJECTS

The intervention used in this study will be the transabdominal, non-invasive fECG.

## Investigational product

The fECG is a non-invasive, transabdominal research method. It uses multiple electrodes on the maternal abdomen to determine the fetal heart rhythm and some parts of the heart’s electrical conduction system.

The pregnant women will be lying down on a comfortable bed in semi-recumbent position. The fECG is conducted with eight electrodes placed on the abdomen, in a fixed configuration. Before applying the electrodes on the abdomen, the skin will be scrubbed to optimize the impedance. On the right side of abdomen a ground electrode is placed.

[figure not shown]

Figure 1: the configuration of the electrodes on the maternal abdomen^1^.

The eight electrodes give bipolar signals of which the fECG comprises. The placement of the electrodes is chosen in order to assess the fetal heart with as much accuracy as possible, as seen in figure 1. Because the fetus can move freely in the uterus, as large as possible number of ECG signals/electrodes is preferred. With eight electrodes, at least some of the electrodes will be close by the fetal heart and thus will give a usable bipolar signal. With this amount of electrodes, we will be able to detect the bipolar signals of the fetal heart in any circumstance. The fECG consists of a 12 – lead signal.

As mentioned in chapter 2, the ECG signals are stored and digitized by a system named the NEMO system, which comprises of a programmable amplifier for the acquiring of electrophysiological signals and a PC for the controlling of the settings of the amplifier and storage of the recordings. This amplifier is based on the M-PAQ (Maastricht Instruments BV, the Netherlands) and modified to maximize the performance^1^.

# 6. METHODS

## Study parameters/endpoints

### Main study parameter/endpoint

In the cross-sectional study, the main study parameter is the determination of the normal value or range of amplitude and segment intervals with 95% confidence intervals of the fECG of a healthy fetus.

### Secondary study parameters/endpoints (if applicable)

The case-cohort study focuses on the abnormal value or range of amplitude and segment intervals in fetuses with diagnosed severe CHD, and compares these with the values found in the cross-sectional study.

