# 3. STUDY DESIGN

Both the cross-sectional and case-cohort study are prospective in nature. In the future, a longitudinal cross-sectional study can be performed based upon this study.

The cross-sectional study will take place in the MMC, Veldhoven, the Netherlands and Diagnostic center Eindhoven, the Netherlands. All the patients who visit the outpatient clinic for the first time will receive information about the research. Patients who visit the Diagnostic center Eindhoven will receive information about the research via their appointment confirmation e-mail. Measurements will be performed before or after the SEO or GUO-1 after written informed consent; patients do not have to come to the hospital or the diagnostic center for an extra visit.

The case-cohort study will take place in the MMC Veldhoven, and the medical centers Radboud MC Nijmegen, Academic Medical Center Amsterdam, and Maastricht UMC the Netherlands. Whenever a patient is diagnosed with a fetal severe CHD in any of these centers by using the SEO and the GUO, they will inform the patient about our research and contact us after informed consent. We will perform a fECG during routine follow up visits in those centers. For more information on recruiting the patients, see chapter 9, paragraph 9.2 “Recruitment and consent”.

In the cross-sectional study, 200 pregnant women will be included. With this amount of patients, we can determine with the wanted accuracy what the normal values and 95% CI of a healthy fetus are^9, 10^. If any of these fetuses is diagnosed with a CHD, they will automatically be evaluated in the case-cohort study.

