In the case-cohort study, we will include pregnant women carrying fetuses with a form of severe CHD, preferably with the same CHD. A severe CHD is defined as possibly life threatening and/or needing intervention or surgery in the first year of life. For now, we believe that of every CHD, we need 10 patients to determine the difference between the normal values and the segment intervals of the fetuses with this severe CHD. The overall incidence of CHD is 4 to 9 per 1000 living newborns^4^. Because of this low incidence, it would take years to include more than 10 fetuses per form of severe CHD. Because of this reason, plus the fact this concerns a pilot study, we chose to include 10 fetuses per form of severe CHD. Because of this low incidence, collaboration with more than one center is needed. We believe that we will be able to collect data of the fECG of 10 fetuses with the support of the other centers.

The fECG signals are stored and digitized by a program named the NEMO system^1^. More details can be found in chapter 4.

With the collected data, we will perform several sub-analyses. We will calculate the normal values and ranges of the amplitudes (P, QRS, T), and the segment intervals with 95% confidence intervals. We will also evaluate the heart axis of the fetus. This data will be compared with the collected data of the fetuses with CHD. The patients will not be notified of any abnormal findings on the fECG, because this contains a pilot study and any findings on the fECG are still being evaluated. Therefore, this research does not have any consequences for the standard care plan of the patients and their fetuses.

If any of the fECG turns out to be abnormal, it will not influence the treatment of the fetus. The main reason for the last fact is that we do not know if the findings we think are abnormal are actually abnormal. This is one of the aspects we would like to investigate.

In the future, a longitudinal research is needed to determine the sensitivity and specificity of fECG.

Approximately 10 weeks postpartum, the patients from the cross-sectional study will receive a questionnaire about their delivery and their newborn and patient information can be withdrawn from the postnatal clinic or the attending pediatrician. If the participants do not return the questionnaire, they will be excluded from further analyses.

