# 8. STATISTICAL ANALYSIS

The collected data will be analyzed through SPSS 19 and two different outcome values will be calculated. The different outcome values are:

- Mean and standard deviation of segment intervals (PQ, QRS, ST etc.) with 95%

confidence intervals

- Mean and standard deviation of amplitudes of the P – top, QRS complex and the

T – top with 95% confidence intervals.

- The heart axis of the fetus

After analysis of these sub-groups (fetuses with the same form of severe CHD in one group, all the healthy fetuses in one group) in SPSS, the different intervals of the fECG of the cross-sectional study and the case-cohort study will be compared with one another through a t-test or a Mann-Whitney-Wilcoxon-test to investigate whether or not there is a repetitive pattern to be recognized. This depends from the normal distribution and the quantity of the collected data. The research is quantitative.

The questionnaires will be analyzed. We will evaluate per fetus if the conducted data from the cross-sectional population is usable and if the data of this particular patient should be excluded due to a missed diagnosis of congenital heart disease during the pregnancy.

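### With about 10 fetuses per CHD form, a CHD range is not usable as a reference range, and the planned comparison tests for a difference without estimating it

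*Protocol*

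**What the plan says.** Section 6.1.2 defines the secondary endpoint: "The case-cohort study focuses on the abnormal value or range of amplitude and segment intervals in fetuses with diagnosed severe CHD", to be compared with the values from the healthy fetuses. The wording parallels section 6.1.1, which sets a normal value or range for the healthy group. Section 6.1.2 does not say that this is done per form. That comes from section 8, which puts fetuses with the same form in one group and all healthy fetuses in another.

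On numbers, section 4.1 says: "Therefore, we will include 10 patients in every CHD group, leading to a total of 60 patients with 6 different forms of severe CHD". For the healthy group, section 3 says: "In the cross-sectional study, 200 pregnant women will be included".

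On purpose, section 3 gives the belief, for now, that for each CHD "we need 10 patients to determine the difference between the normal values and the segment intervals of the fetuses with this severe CHD". Section 4.1 limits the ambition: "We believe this will be enough to detect any big differences between the fECG of the healthy fetuses and the fECG of the fetuses with" the heart defect, and it adds that more research will be needed. Section 4.4 drops that limit: "we believe that a total of 10 patients per severe CHD will be enough for the evaluation and the comparison". It also discloses that the CHD numbers rest on no sample size calculation, because this part is a pilot.

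On analysis, section 8 lists means and SDs of intervals and amplitudes with 95% confidence intervals. It then compares the groups by a t-test or a Mann-Whitney-Wilcoxon test "to investigate whether or not there is a repetitive pattern to be recognized". No confidence interval for the difference between a CHD form and healthy is named.

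**The concern.** There are two mismatches between what the protocol wants from the CHD part and what it sets up.

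First, the same kind of quantity, a value or range, is named for 200 healthy fetuses and for groups of 10, with no distinction between them. The outer limits of a distribution are much harder to estimate than its centre, and 10 observations say little about them. A reader who compares a CHD range with the healthy range needs to know that the two are not of similar quality.

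Second, section 3 says the 10 fetuses are there to determine a difference, but section 8 only tests whether one exists. A test result gives neither the size of a difference nor how well it is known. With 10 fetuses on one side, a non-significant result is compatible with differences of moderate size, and nothing in the protocol says so.

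At stake is how the secondary results can be interpreted and used to plan the later research the protocol foresees. The primary aim is not affected.

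**Working it through.** **Inputs.** 10 fetuses per CHD form (section 4.1) and 200 healthy fetuses (section 3). The protocol gives no SD, effect size, alpha or power. Assumed: normal data, equal SD in both groups, two-sided alpha 0.05, effects in SD units over a range of sizes. There is no stated precision or power to reproduce. The only figure that can be checked is 6 forms × 10 = 60, which agrees with section 4.1.

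**1. Precision of a range limit.** For a 95% range taken as mean ± 1.96 SD, the standard error of one limit is SD × √(1/n + 1.96²/(2(n − 1))).

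- n = 10: √(0.1000 + 3.8416/18) = √0.3134 = 0.560 SD; 95% half-width 1.96 × 0.560 = ±1.10 SD.
- n = 200: √(0.0050 + 3.8416/398) = √0.01465 = 0.121 SD; half-width ±0.24 SD.

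The limit from 10 is about 1.10/0.24 = 4.6 times less certain.

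**2. What a range from 10 would contain.** By simulation, a nominal 95% range (mean ± 1.96 SD) from 10 fetuses covers 90.5% of the population on average, and about 74% or less in 1 sample of 20. From 200 the average is 94.8%. If range means the observed minimum to maximum, its coverage follows a Beta(n − 1, 2) distribution. For n = 10 the mean is 9/11 = 82%, and 95% coverage is reached in only 9% of samples. A minimum-to-maximum range that covers 95% of fetuses with 95% confidence would need 93 fetuses per form.

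**3. Precision of the difference.** For 10 against 200, SE = √(1/10 + 1/200) = √0.105 = 0.324 SD. With 208 degrees of freedom (t = 1.971) the 95% half-width is 1.971 × 0.324 = ±0.64 SD. This is wide, but it can be interpreted.

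**4. Power of the test, 10 against 200.** The t-test figures use the noncentral t distribution; the Mann-Whitney figures are simulated.

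| True difference | t-test | Mann-Whitney | Missed by the t-test |
|---|---|---|---|
| 0.5 SD | 34% | 32% | 66% |
| 0.8 SD | 69% | 67% | 31% |
| 1.0 SD | 87% | 84% | 13% |
| 1.2 SD | 96% | not run | 4% |

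The difference detectable with 80% power is 0.91 SD. If exclusions for unreturned questionnaires reduced the healthy group to 150 (an assumed 25% loss), it would be 0.92 SD, so the 10 drive the result.

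These figures are for one parameter and one form, unadjusted. With six forms tested on one parameter, the chance of at least one false positive is 1 − 0.95⁶ = 26% if the tests are independent. With a Bonferroni correction over six, power at 1.0 SD falls to 66% and the difference detectable with 80% power rises to 1.14 SD.

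**The case against.** The case on the other side is substantial. Section 6.1.2 says value *or* range, so a range is only one alternative, and section 8 plans no percentiles or reference limits for the CHD groups. The calculations on range limits therefore apply only if the range option is used. The CHD part is openly a pilot, with 10 per form chosen because of low incidence and no sample size calculation claimed. An interval for a difference is also a detail often left to a statistical analysis plan, which may exist.

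Three stronger readings are tempting, and the protocol does not support them.

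- *Section 8 delivers nothing but a test verdict.* It also lists means and SDs with 95% confidence intervals and refers to analysis of the sub-groups. What is missing is the interval for the difference.
- *Ten fetuses are too few for any comparison.* Section 4.1 aims at large differences, and for a true difference of 1 SD or more the unadjusted power is 87% or higher. Quoting only the 34% at 0.5 SD would judge the test against a target that section 4.1 does not set, although section 4.4 calls 10 enough without that limit.
- *The results will be published misleadingly.* That is a forecast. The wording about a repetitive pattern states a purpose; it is not a rule that non-significance means no pattern.

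What remains is that the endpoint wording still permits a CHD range, and the named comparison still does not estimate what section 3 says the 10 are for. Both are fixed in the protocol itself. The pilot status supports estimation with intervals over a yes/no test.

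**Conclusion.** The point holds as an inexpensive improvement to a secondary, exploratory aim. A range from about 10 fetuses, with each limit uncertain by ±1.10 SD, is not usable as a reference range for a CHD form. The 10-against-200 test is reasonable for large differences, but it misses about 31% of true differences of 0.8 SD and 66% of those of 0.5 SD. A non-significant result therefore cannot be read as absence of a pattern. The per-form difference with its 95% interval, about ±0.64 SD, answers the question in section 3 directly and shows its own uncertainty.

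These sizes rest on normal data, equal SDs, two-sided 5% tests without adjustment, and full groups of 10 and 200. How large the real differences are in SD units cannot be judged from the protocol.

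**What to change.** - **Section 6.1.2:** for the CHD groups, delete the words *or range*, or state that any range shown is the observed values only and not a reference range. Define the comparison as the difference between each CHD form and the healthy group.
- **Section 8:** name each form's difference from healthy, with its 95% confidence interval, as the main exploratory result, and keep the t-test or Mann-Whitney test as secondary. Add that a non-significant test is not evidence that a form has no pattern.
- **Section 4.4:** repeat the limit to large differences from section 4.1, so that the two statements about 10 being enough agree.

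Plotting each CHD fetus against the healthy reference range, or expressing differences in units of the healthy SD, would help readers but is optional.

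The cost is a few sentences. No extra patients, measurements or visits are needed. The downside is a more modest claim for the CHD part.

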## Randomization, blinding and treatment allocation

There will be no randomization or blinding.

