## Study procedures

All the patients will undergo a non – invasive, transabdominal fECG during regular outpatient clinic appointments, performed by one of the researchers. This test has a very low grade of discomfort for the patient. The conducted fECG will be stored on an external hard drive, the data will be analyzed by researchers of the Technical University. The last two investigators will look at the fECG and will determine the segment intervals, the heart axis and the amplitudes. After the analysis, we will be able to enter the data in SPSS to conduct normal values and ranges with 95% confidence intervals. The patients will not be notified of any abnormal findings on the fECG, because this is a pilot study. We do not know for certain that any abnormalities we find are actually real abnormalities. This is something we want to investigate.

In the cross-sectional study, we want to know if the fetuses we included are born healthy. Therefore, we will evaluate this with a simple questionnaire which we will send four to six weeks postpartum. We believe this questionnaire will be sufficient to evaluate if any severe CHD was present at birth, because a severe CHD has hemodynamic consequences which present early in neonatal life. Besides, we have permission to withdraw patient information at the postnatal clinic or attending pediatrician. If the neonate has a congenital heart disease missed by the SEO, we will exclude the patient from the cross-sectional study and will evaluate the data of the fECG in the case-cohort study. If the participants do not return the questionnaire, they will be excluded from further analyses.

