# 10. ADMINISTRATIVE ASPECTS, MONITORING AND PUBLICATION

## 10.1 Handling and storage of data and documents

The data will be stored in a computer program named the NEMO system. This program can digitize and store the data of the fECG. The data will be coded, stored on a hard disk and will be handled with care. The patients will be numbered. Only the principal investigator will have the key to the code. The data will be kept for 15 years after termination of this study.

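### Section 6.2 excludes all blinding, and nothing else keeps the fECG readers unaware of CHD status, which leaves the secondary healthy-versus-CHD comparison open to expectation-driven reading

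*Protocol*

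**What the plan says.** Section 6.2 consists of one sentence: "There will be no randomization or blinding". It is unqualified.

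Section 6.3 describes how the measurements arise. The recordings are stored, and "the data will be analyzed by researchers of the Technical University". It continues: "The last two investigators will look at the fECG and will determine the segment intervals, the heart axis and the amplitudes". The values then go into SPSS. The section mentions no automated measurement.

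Section 10.1 says the data are coded: "The patients will be numbered. Only the principal investigator will have the key to the code". It does not say whether the number hides the study part, the centre or the diagnosis from those who read the trace.

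The inclusion criteria for the case-cohort study require a "Pregnant woman carrying a fetus with a known severe CHD", so CHD status precedes the recording. Section 8 compares each CHD group with the healthy group by a t-test or a Mann-Whitney-Wilcoxon test. Section 2 has the diagnostic value of the fECG as a secondary objective, and section 8.2 has typical fECG patterns in severe CHD as the secondary parameter.

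**The concern.** The readings are a human judgement on a weak signal. Section 1 lists the reasons: distance through maternal tissue and amniotic fluid, a moving fetus, a heart about one tenth of adult size at 20 weeks, and the normal dominance of the right ventricle. The same section calls the heart axis the most important aspect of the ECG and says right axis deviation occurs in most severe forms. A reader who knows the diagnosis thus has both room for judgement and an expected answer.

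A reading error that differs between healthy and CHD recordings enters the group comparison directly, and no later analysis can separate it from a real difference. It also weakens the diagnostic-value objective, because the test under study would have been read with knowledge of the reference diagnosis. The protocol says it wants to learn whether apparent abnormalities are real. Unmasked reading makes that question harder to answer.

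**Working it through.** **Does any part of the protocol mask the readers?**

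- Section 6.2 excludes blinding without exception.
- Section 6.3 has investigators look at the trace and determine the values. It does not say what they know about the fetus.
- Section 10.1 numbers the patients and leaves the key with the principal investigator. This protects identity. Nothing extends it to study part, centre or CHD type.
- Sections 3 and 9.2 have CHD patients recruited after diagnosis, at named centres. The healthy cohort comes from MMC Veldhoven and Diagnostic center Eindhoven. A file that shows its centre could therefore reveal its group.

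No section keeps the reader unaware of CHD status.

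**Which results are exposed?** The primary parameter (sections 6.1.1 and 8.1) describes one presumed-healthy cohort, so differential reading has no contrast to distort. The secondary comparison, the typical patterns and the diagnostic value all rest on healthy and CHD readings taken together.

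**How large could the effect be?** The protocol states no alpha, SD, effect size or reader-bias figure, so there is no figure of its own to reproduce. What follows is an illustration.

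Inputs from the protocol: 200 healthy fetuses (section 3) and 10 per CHD form (section 4.1).

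Assumptions: two-sided 5% t-test, equal SD in both groups, no true difference, and a systematic reading shift of *b* SD in the CHD group.

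- Degrees of freedom: 200 + 10 − 2 = 208; critical value 1.971.
- Standard error in SD units: √(1/200 + 1/10) = √0.105 = 0.324.
- Noncentrality: *b* / 0.324.
- False-positive rate: the sum of both rejection tails of the noncentral t distribution.

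| Assumed shift *b* (SD) | Noncentrality | False-positive rate per test |
| --- | --- | --- |
| 0 (masked) | 0 | 5.0% |
| 0.1 | 0.309 | 6.1% |
| 0.2 | 0.617 | 9.4% |
| 0.25 | 0.772 | 12.0% |
| 0.5 | 1.543 | 33.6% |

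For scale, the smallest true difference that this comparison detects with 80% power is about (1.960 + 0.842) × 0.324 = 0.91 SD. A shift of 0.5 SD is a little over half of that. These rates are per test, and section 4.1 plans six CHD groups with several parameters each.

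**The case against.** The strongest reply is that the documents do not show readers are told the diagnosis. Section 6.2 carries a template heading and does not mention fECG readers, and section 10.1 codes the data. This stands as a limit on the claim: bias is possible, not demonstrated. It does not remove the point, because section 6.2 disclaims blinding outright and nothing says the code hides the group.

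Some details are also inference. The protocol does not use the words 'by hand', and it is not clear who the two investigators in section 6.3 are, perhaps because names were removed. Appendix II, which lists ECG findings by lesion, comes from a paediatric source and mostly names hypertrophy, block and axis patterns. It is weak evidence of what a reader would expect for a fetal interval or amplitude. The expectation is clearest for the axis, which section 1 itself names.

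The protocol also calls the case-cohort part a pilot with no sample size calculation. That lowers the stakes, but reading bias in a pilot can still create the pattern that later work sets out to confirm.

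A reader might go further and take section 8 ("We will evaluate per fetus if the conducted data from the cross-sectional population is usable") as an unmasked signal-quality exclusion that could trim the tails of the normal range. The text does not support this. The sentence follows the statement that the questionnaires will be analysed, and it continues to exclusion for a missed diagnosis. It reads as a postnatal eligibility check, which must use the diagnosis. It covers only the healthy cohort because section 6.3 gives the questionnaire only to that cohort.

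**Conclusion.** The point holds in a limited form. The protocol rules out blinding and has no provision that keeps fECG readers unaware of a CHD diagnosis known before recording. This exposes the secondary comparison, the typical-patterns parameter and the diagnostic-value objective. It would be wrong to infer that every endpoint is compromised: the primary normal ranges are touched at most by readers knowing that the fetus is presumed healthy.

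The size is unknown. The range of about 6% to 34% false positives per test, for shifts of 0.1 to 0.5 SD, rests on an assumed shift, an assumed 5% two-sided test and equal SDs. It shows what such a bias would do, not that one exists. This is a worthwhile, inexpensive improvement to make before the traces are read, because it cannot be made afterwards. It is not a flaw that invalidates the study.

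**What to change.** Replace the sentence in section 6.2 with:

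> No randomization. Investigators who determine intervals, amplitudes and axis are masked to study part, CHD type, centre and postnatal outcome. Recordings are supplied in mixed order under neutral numbers, and the key stays with the principal investigator until the values are locked.

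Leave the questionnaire-based exclusion in section 8 unchanged. Patients and the person making the recording need not be masked. The protocol does not say whether a recording researcher or the key holder also reads traces. The masking works only if the readers are neither, so section 6.3 should make this clear.

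Cost: someone must strip, relabel and mix files from several hospitals, and CHD files must wait until they can be batched with healthy ones. No extra patient, visit or recording is needed. Because section 3 says fECG findings do not influence care, the wait has no consequence for the fetus.
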